### Questionnaires

As part of the study, participants complete a series of four separate baseline questionnaires: two at home prior to arrival to the laboratory (Socioeconomic and Psychological Survey) and two sets of questionnaires (Physical Activity Survey and Biomechanical Survey) in the laboratory.

The Socioeconomic Survey, prepared in collaboration with the study partner of Program 1 of the HAIE project (Faculty of Medicine at the University of Ostrava), consists of questions about sociodemographic factors, basic lifestyle factors, risk perception, health status, and quality of life. The completion of the survey takes approximately 40 min. The Psychological Survey includes questions concerning psychological protective factors (such as social support) and risk factors (such as perceived stress, depressive symptoms, or neuroticism). Questions about sleep are also included. The completion of the survey takes approximately 30 min. The Physical Activity Survey completed in the laboratory is composed of questions about physical activity, sedentary behavior, motivational and psychological factors associated physical (in) activity and running history. The completion of the survey takes approximately 45 min. In the Biomechanical Survey (20 min) participants are asked about injury history and pain. A detailed summary of the questionnaires and measures used in this study can be located on the study website https://www.4haie.cz/data/.

At month 6 and month 12, participants are asked to complete a subset of selected measures online from home again. The completion of each of the follow-up surveys takes approximately 45 min.

### Hair samples

Until a few years ago, cortisol has been analyzed only from blood, saliva or urine to assess acute or short-term circulating cortisol concentrations [66]. Whereas these acute and transient cortisol reactivity are part of the adaptive response to challenge and generally unharmful [67], long-term secretion of the cortisol is considered to play a crucial role in mediating the link between chronic stress and negative effects on physical and mental health [68]. Given the possible negative health effects of chronic long-term stress, in this study we use a new non-invasive, easily conducted and well tolerated method of analysis of cortisol from hair samples. Three-cm segment of hair is collected by a trained person with small scissors as close to scalp as possible, according to a validated protocol [69]. Hair samples are taken from the posterior vertex region in accordance with guidelines published by the *Society of Hair Testing* [70]. Considering that hair grows approximately 1 cm per month [71], hair samples are obtained in order to evaluate hair cortisol levels representative of the last 3 months [72]. Each sample is wrapped in aluminum foil to protect it from light and humidity and stored in closed plastic bags (marked with the ID, date and initials of laborant) at room temperature. Later, the samples will be analyzed at the Dresden University of Technology, Germany using an Enzyme-Linked Immunosorbent Assay (ELISA), a reliable and valid method to assess hair cortisol levels, which is highly positively correlated with liquid chromatograph–mass spectrometry (LC–MS/MS) [73].

### Cognitive assessment

The neurocognitive session includes five tests assessing memory, language and executive function:

#### Rey auditory verbal learning test (RAVLT) [74]

RAVLT is a powerful neuropsychological tool that is used for assessing episodic memory by providing scores of evaluating different aspects of memory including immediate recall, short-term and long-term memory, and verbal learning. The participant is required to learn a list of 15 words presented verbally at 2-s intervals over the course of 5 trials and recall verbally as many of the words as possible in any order after each trial. After approximately 30 min participants are asked to recall the words without repeated presentation to assess the long-term memory. The RAVLT is sensitive to verbal memory deficits caused by variety of neurological conditions [75].

#### Verbal fluency test [76]

We use 2 measures of verbal fluency, phonemic and semantic. Participants are asked to recall verbally as many words beginning with S, K and P (phonemic fluency) and as many animal names (semantic fluency) as they can. Sixty seconds is allowed for each of the 4 tests. Verbal fluency is used to investigate the presence of cognitive impairment, neurodegenerative and psychiatric conditions [77].

Three computerized tests from *NIH-Examiner battery* developed to reliably and validly assess domains of executive function [78]: Flanker Attention test, Set Shifting task, and Nback and 2Nback tests. Tasks are applicable to a broad range of individuals from different age and ethnic groups. Flanker task is a response inhibition task used to assess the ability to suppress responses that are inappropriate in a specific context; Set shifting task assesses cognitive flexibility and Nback and 2Nback assess working memory. During these tasks frontal brain structures are thought to be activated [78] . We used back translation method to translate the tests into the Czech language. Each participant completes these 3 tasks on laptops in the Psychopy program (version 1.73) [79].

### Neuroimaging

Scanning is carried out at the Department of Human Movement Studies, University of Ostrava, using a 1.5 T Siemens Magnetom Sempra Scanner with a 16- channel head coil (1.5 T Siemens Magnetom Sempra Scanner; Siemens, Erlanger, Germany). The neuroimaging protocol comprises structural sequences only, lasting approximately 10 min. MRI sequences include high-resolution T1-weighted, T2-weighted and 3-scan trace diffusion-weighted imaging. A full description of the MRI parameters adopted in our sequences is provided in Table 2. Cortical surface reconstruction and subcortical segmentation is completed via FreeSurfer (version 6.2), including total grey and white matter as well as subcortical volumes, cortical thickness and cortical surface area estimates for cortical regions [80]. Images undergo quality control prior to processing by 3 experts: a radiologist with 10 years of experience and two image analysts, each with 2 years of experience. Brain tissues and subcortical regions are visually inspected to ensure an accurate segmentation, gauge the severity of motion, intensity homogeneity, white matter underestimation, pial overestimation and artifacts [80]. Quality control of FreeSurfer reconstructions is based on MELD Protocol 3 [81].

**Table 2 Tab2:** Set up of the MRI protocol used in the study

MRI sequences and parameters				
Imaging parameter	3D T1 MPRAGE	Axial T2 TSE	Axial T2 Dark fluid TSE FS	ep2d diff 3scan trace
Repetition time (ms)	2200	3200	7910	4800
Echo time (ms)	2.72	91	83	113
Inversion time (ms)	900	–	2359	–
Slice thickness (mm)	1	4	4	5
Field of view (mm)	256	230	215	230
Matrix size	197 × 256	210 × 320	179 × 256	176 × 176
Flip angle (°)	8	150	150	–
Bandwidth (Hz/Px)	160	191	190	812
Echo train length	–	7	4	–
Signal average	1	2	2	–
Number of slices	192	34	34	20
Acquisition time (min:s)	3:39	1:38	2:24	1:23

*MPRAGE (Siemens)* Magnetization Prepared – Rapid Gradient Echo; *TSE* Turbo Spin Echo, *FS* Fat Saturation

### Long-term monitoring and EMA protocol

Following baseline assessments, participants are monitored for 12 months using the Fitbit Charge 3 monitor. Additionally, participants complete brief surveys administered on their smartphones through a mobile app developed for the study. The intensive assessment incorporates elements of ecological momentary assessment (EMA) and will be administered four times for 2 weeks across the 12-month period (at baseline, month 4, month 8, and month 12). In an EMA study, participants are usually prompted several times during the day or are asked to self-initiate a report when an event occurs. This largely reduces the risk of retrospective recall bias associated with summative judgements or recollection of behavior patterns [61]. EMA performed on smartphones has a number of advantages including automatic recording of the time stamp of answers in near-real-time, possibility of tracking of compliance and response patterns, and possibility of combining survey responses with other data such as those from a connected monitoring device (here the Fitbit Charge 3 monitor) or other data from the smartphone device or from other online sources.

In this study, participants complete four 14-day bursts of EMA data collection. Four pseudo-random surveys (sampling four daily periods: 8–11:59, 12–15:59, 16–19:59, 20:00–22:00) assess momentary variability in affective states, stress, pain, and context. The morning survey includes questions about sleep and the evening survey (last of the day) also includes some retrospective end-of-day assessments. Additionally, participants are asked to complete two types of self-initiated reports: (1) PA report (episodes of intentional PA lasting at least 20 min and leading to increased heart rate, breathing and sweating) and (2) injury report (when encountering injury associated with physical activity). Every Sunday between 16:00 and 20:00 participants also receive a weekly injury survey (to facilitate prospective monitoring of injury incidence even in cases when a self-initiated injury report may not have been filed). This weekly survey was also enriched by COVID-19 related questions during the pandemic restrictions to evaluate factors associated with PA and mental health (for details please see description at https://www.covidminds.org/longitudinal-studies; The 4HAIE study). Finally, a context-trigged survey is initiated when Fitbit data indicate a decrease in PA in a given week below 90% confidence interval of the average level of the past 4 weeks. This floating algorithm allows us to detect potential periods of decline in PA that may also be indicative of incurred injury.

In this study, we also collect real-time data about air quality from a network of available public air quality measurement stations. A server application developed for the study specifically aggregates publicly available data on all available air pollution parameters (data downloaded every 30 min) and integrates them with GPS data obtained from the smartphone while protecting participant privacy. Exact GPS location of participants is not recorded, only data from the linked nearest public air quality monitoring station is used each time they make a report of an episode of PA or at least once per day when no activity is reported. Monitoring and combining these different streams of data will allow us to evaluate dynamically the associations among air pollution parameters, behavior and wellbeing, and so gain rich insight into patterns of healthy functioning and within-person fluctuations of variables of interest across moments, days, or weeks. Figure 2 depicts the overview of the entire study protocol including the EMA bursts.

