Herein, we describe the behavioral, psychological, and neuroimaging aspects of the study protocol from Program 4 of the Healthy Aging in Industrial Environment (HAIE) project, including how mobile technology is utilized to collect real-time data on air quality, behavior, and daily psychological functioning. HAIE consists of four research programs that are interlinked using the same selected population groups study the impact of individual and environmental determinants of health, wellbeing and healthy aging. Program 4 of the HAIE project (4HAIE) specifically focuses on the links between air pollution, biomechanical, physiological, psychosocial, and sociodemographic variables (and their interaction) on the incidence of running-related injuries, physical (in) activity, health and quality of life. Herein, we describe the protocol for the assessment of behavioral, psychosocial and neurocognitive outcomes as part of the study, including key domains of interest in the relationship between air pollution, selected behavioral parameters, psychological functioning and neuroimaging correlates.

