**Fig. 1 Fig1:**
[figure not shown]
Field of annual average concentration of PM2.5 in 2018 indicating limit value valid from 2020_._ The figure was adapted from publicly available source with author permission (Air Quality Information System. Air Pollution in the Czech Republic in the year 2018. 2018. https://www.chmi.cz/files/portal/docs/uoco/isko/grafroc/18groc/gr18cz/PrilohaII_CHMU2018.pdf. Accessed 22 Jun 2020)

For the 4HAIE study, specifically, the recruitment of study participants was commissioned to a professional social science research and marketing company selected through a publicly advertised tender. The sample is collected using quota sampling based on location, age, gender, and PA status (active-runner vs. inactive) (for details see Table 1).

**Table 1 Tab1:** Recruitment quotas based on age, region (SBR = South Bohemian Region, MSR = Moravian-Silesian Region) and activity status

Age group	Runners (60%)		Inactive Controls (40%)	
	SBR	MSR	SBR	MSR
18–25	90	90	60	60
> 25–35	90	90	60	60
> 35–45	90	90	60	60
> 45–55	90	90	60	60
> 55–65	90	90	60	60
Total N	450	450	300	300

A total of *N* = 1500 participants aged 18–65 years will be recruited for this study. Of these, *n* = 900 (60%) will be physically active runners and *n* = 600 inactive controls. The runners and inactive controls will be split evenly between two regions: the experimental highly-polluted industrial region (Moravian-Silesian Region – with the exception of the district of Bruntal and selected counties in the district of Frydek Mistek) and the control low-pollution level region (South Bohemian Region). The selected sample size was determined as the largest sample size feasible, allowing for stratification of the cohort by age group and analysis of outcomes targeted by the interdisciplinary teams involved. No formal unifying power analysis was however conducted.

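### Pollution readings are triggered by reported physical activity, which is also an outcome, so short-term pollution-activity models built on those readings can be biased; the protocol should fix one exposure window for all days

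*Protocol article*

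**What the plan says.** Under Methods, Long-term monitoring and EMA protocol, a server collects public station data independently of what participants do ("data downloaded every 30 min"). The link to a person is narrower: "Exact GPS location of participants is not recorded, only data from the linked nearest public air quality monitoring station is used", and this happens "each time they make a report of an episode of PA or at least once per day when no activity is reported". No clock time is given for days without a report.

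PA reports are self-initiated and cover "episodes of intentional PA lasting at least 20 min and leading to increased heart rate, breathing and sweating".

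The same section says that combining these streams "will allow us to evaluate dynamically the associations among air pollution parameters, behavior and wellbeing", and gives the time scale as "within-person fluctuations of variables of interest across moments, days, or weeks". The Present Study section lists PA among the outcomes: the programme studies effects "on the incidence of running-related injuries, physical (in) activity, health and quality of life". No exposure window common to days with and without a PA report is stated.

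**The concern.** An exposure should be measured in the same way whatever the outcome. Here a day with a PA report carries one or more readings tied to reports that the participant chose to make, from wherever the participant then was. A day without a report carries at least one reading at an unstated time. If pollution has a daily cycle, or differs between where people exercise and where they otherwise are, the two kinds of day show different measured pollution even when pollution has no influence on activity. A PA bout that goes unreported is treated, for linkage, as a day without activity.

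Mood and sleep models are exposed to the same problem less directly. The Background notes that activity and sleep covary with wellbeing, so a reading whose timing follows activity carries an error that can correlate with mood.

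What is at stake is the within-person, short-term part of the study. The Present Study section offers this part as the advance over earlier work that used annual averages and could not detect acute change.

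**Working it through.** There is no planned figure to reproduce: the article says "No formal unifying power analysis was however conducted" and states no effect size for this question. The check asks whether the capture rule alone can create an association.

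**Inputs from the article.** The linkage trigger, the 30-minute station data, and four 14-day EMA bursts, so 4 × 14 = 56 days per person.

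**Assumed inputs (not in the article).** 300 persons; about half of days active; log daily pollution with SD 0.5; reading noise SD 0.15; cosine daily cycle on the log scale with amplitude A, peak at 03 h and trough at 15 h. PA readings fall around 7, 17 or 20 h (SD 1.5 h). No-report readings fall at 0, 8, 12 or 14 h or at a random hour. One reading per day is used as the regressor for active versus inactive day.

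**Formula.** With no true effect and roughly normal readings, the log odds ratio per 0.5 log units is about 0.5 × Δ / σ². Δ is the mean log difference between readings on active and inactive days, and σ² = 0.5² + 0.15² = 0.2725. The spread of PA times multiplies the cosine by exp(−(2π × 1.5/24)²/2) = 0.926. For A = 0.2:

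- PA at 7 h against noon: Δ = 0.2 × (0.926 × 0.500 + 0.707) = 0.234. OR = exp(0.5 × 0.234/0.2725) = 1.54 (simulated 1.56).
- PA at 17 h against midnight: Δ = 0.2 × (−0.926 × 0.866 − 0.707) = −0.302. OR = exp(−0.554) = 0.57 (simulated 0.57).
- PA at 17 h against noon: Δ = 0.2 × (−0.802 + 0.707) = −0.019. OR = exp(−0.035) = 0.97 (simulated 0.95).

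The same formula covers place. If stations linked on active days read 0.1 log units higher, a factor of exp(0.1) = 1.105, then OR = exp(0.5 × 0.1/0.2725) = 1.20 with no true effect.

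**Simulation results**, as the range over seven pairs of reading times, logistic model, OR per 0.5 log units:

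| A | Triggered reading, no effect | Triggered reading, true OR 0.82 |
|---|---|---|
| 0 | 0.98 to 1.03 | 0.81 to 0.85 |
| 0.1 | 0.75 to 1.27 | 0.65 to 1.00 |
| 0.2 | 0.57 to 1.56 | 0.47 to 1.27 |
| 0.4 | 0.34 to 2.30 | 0.27 to 1.93 |

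A = 0.2 means a peak-to-trough ratio of exp(0.4) = 1.49. At that amplitude a true OR of 0.82 is reversed to 1.27 (7 h against noon) and to 1.11 (20 h against 14 h).

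A daily level defined identically on every day gave 0.97 to 1.02 under no effect and 0.79 to 0.85 under the true 0.82. The standard error of the log OR is about 1/√(300 × 56 × 0.25) = 0.015, so this spread is about what simulation noise produces.

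**The case against.** The strongest reply is that the sentence describes how a phone is tied to a station while protecting privacy, not the exposure variable of any model. Averaging window and lag are commonly left to the full protocol or analysis plan, and neither is shown. That stands in part: nothing says that one spot reading will be the day's exposure. But the article does say that station data are used at these moments and for these associations. Nor is a capture rule wholly repairable later. With no location stored, a station link that was not made on a given day cannot be rebuilt.

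Several stronger readings are tempting but unsupported:

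- *Inactive days get a single reading at a default hour.* The text sets a minimum of one and names no hour.
- *The reading does not belong to the bout.* The content of the PA report is not described, so it may ask for the bout time.
- *The bias can never be signed.* If reading times are stored, the timing part can be examined and adjusted.
- *The moment-level link with mood is missing.* EMA prompts are not named as linkage times, but EMA answers are time-stamped and could be matched to half-hourly data from a linked station.
- *The odds ratios estimate the bias in this study.* They follow from assumed cycles and clock times. The bias nearly vanishes when there is no cycle or when both readings fall at similar points of it (17 h against noon: 0.94 to 1.01 under no effect). Recovery by the common daily level is also close to built in, because the simulated effect was placed at day level.
- *All PA results are affected.* Fitbit records activity continuously, and that outcome is affected only so far as PA reports coincide with active days. The simulation made trigger and outcome identical, which is the worst case.

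**Conclusion.** The point holds conditionally. The article fixes a capture rule under which the time, number and place of exposure readings depend on reported PA, a named outcome. If those readings are the exposure in within-person models of activity, mood or sleep, variation in pollution over the day or between places can create or reverse an association. Neither size nor sign can be derived from the article; the simulated ranges show only that modest cycles suffice.

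The comparison of the Moravian-Silesian and South Bohemian regions does not use these readings and is unaffected. The problem is therefore confined to the short-term analyses, where it deserves correction because the remedy is cheap and part of the data can no longer be re-linked.

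**What to change.** - **All participant-days.** With or without a PA report, compute exposure over the same fixed window from the half-hourly station data, for example a 24-hour mean plus a fixed daytime window. Use it in every short-term pollution model. Keep bout-time readings for inhaled-dose questions only.
- **Ongoing and future participants.** Record the linked station's identifier, without GPS position, at fixed times on all days and at each EMA prompt, so that station choice is no longer PA-triggered. Averaging over time does not achieve this by itself.
- **Participants already monitored.** Apply the fixed window to a home or usual station. Being constant within a person, it cannot differ between that person's active and inactive days. Report a sensitivity analysis using the linked station.

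**Cost.** Some server and linkage work, assuming that the half-hourly downloads are kept and that a home or usual station can be identified. Residual station-choice bias remains in data already collected wherever the linked station is used, and a home station misses pollution met elsewhere. At the article's November 2020 count, 360 of 1012 participants had finished. Up to 1012 − 360 = 652 enrolled (fewer after dropout) and 1500 − 1012 = 488 still to be recruited could then have gained from the changed capture for all or part of their follow-up.

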**Fig. 2 Fig2:**
[figure not shown]
Graphic overview of the study protocol. *Note*. Figure adapted with permission from the Czech Information System on Air Quality (ČHMÚ). Data are from 2018 and reflecting limit value valid from 2020

## Discussion

Within this protocol, we introduce a unique interdisciplinary study to longitudinally assess the associations among air pollution, physical (in) activity, running-related injuries and psychosocial factors in a sample of *n* = 1500 participants across the adult lifespan (18–65 years). As part of the study, rich laboratory assessments are conducted (on physiological, biomechanical, anthropometric, cognitive and neuroimaging variables) in combination with online surveys (sociodemographic, psychological, physical activity, biomechanical variables) to establish baseline characteristics of the study cohort. These cross-sectional assessments will be followed with long-term follow-up assessments 5 years later (as part of a follow-up project) to allow for detection of risk/protective factors in the context of long-term change. More acute, short-term effects of air pollution and PA status on sleep, psychological and injury parameters can also be evaluated due to the dynamic 12-month monitoring (following baseline assessments) using objective sensory data (Fitbit) and mobile apps. These intensive longitudinal data will enable prediction of *individual trends* in sleep, physical activity, injury risk, and air pollution to help establish suitable future intervention targets.

It is of particular interest in this study to evaluate and detect important predictors of running-related injuries (RRI), including potential differences in incidence rates by air-pollution or PA status. To this end we collect prospective weekly self-report data as well as self-initiated in-time reports of PA-related injuries via the study mobile app. To this date (October 2020), 287 self-initiated reports of occurred injuries have been received from *n* = 171 participants. In weekly reports, 396 individual reports of injuries have been collected from *n* = 261 participants. We have received 7777 at least partially answered PA decrease surveys from *n* = 844 participants (additional 1691 surveys were returned unanswered). These data can be aggregated with other EMA and air pollution data to assess whether there are differential rates of injuries across air pollution and PA status and what psychological, biomechanical, or physiological factors may underlie the differences. There is a lack of RRI studies with dynamic EMA psychosocial data in the literature. Some studies suggest that psychosocial variables can be predictors for RRI. For example, scores on self-reported mental health and negative affect were predictive of injury status in another two-year prospective study, with runners who suffered injury reporting worse mental health status and more negative emotions [82]. In addition, dynamic EMA data from HAIE study may indicate whether variations in psychosocial variables may be serve as meaningful predictors of RRI. This information may aid in future interventions aimed at maintaining recommended levels of PA while minimizing running-related injuries.

Additionally, longitudinal Fitbit data combined with EMA survey data on the context of PA will allow us to evaluate PA decreases throughout the 12-month monitoring period, including decreases unrelated to injuries. While previous studies have focused on predicting the participation and levels of PA [83, 84], little attention has been devoted to studying for instance weekly or monthly fluctuations and decreases in PA. Although some level of PA is better than none and even dose lower than recommended may bring some health-related benefits [85], it is regular and sustained PA that is likely to garner the most positive effects on health and related variables. It is thus important to evaluate the predictors of decreases in PA and fluctuations specifically, to aid future interventions focused on the long-term maintenance of PA.

The integration of mental and neurocognitive assessments and brain MRI in our study, in combination with data on physiological and behavioural variables, may provide relevant knowledge about the association between air pollution and cognitive and brain health outcomes observed in many but not all studies [40, 42–46, 48, 51, 80]. While PA has been long considered a protective factor for dementia, air pollution has been acknowledged as one of the key risk factors for dementia only recently [86]. The interactions between level of PA and air quality have been therefore rather underinvestigated, supporting the importance of our study. Our findings may contribute to the small amount of literature examining the psychological and neurological benefits of regular exercise in non-polluted and polluted environments [57]. Furthermore, due to wide range of PA levels (particularly in the active group), the 4HAIE study may help to unveil whether the potential association between level of PA and mental and cognitive functioning is linear or not. There might be an optimal level of PA beneficial for the brain while extreme levels of PA might be rather ineffective or even detrimental to brain health.

The interdisciplinary approach of our study and multiple laboratory data collection, including blood markers, cardiac autonomic functioning, and brain MRI imaging, will enable us to investigate potential biological mechanisms linking air-pollution and PA status, to mental and cognitive health. We expect cognitive function and specific brain structures such as prefrontal cortex, white matter and hippocampus, to be lower and smaller in volume, respectively, in adults from air-polluted environment and in inactive controls. Our primary plausible physiological mechanisms underlying the association between air-pollution and worse mental and cognitive health are higher level of chronic inflammation and oxidative stress, lower level of BDNF, and cardiac and vascular functioning [52].

In a longitudinal perspective, based on laboratory data collected in future waves, this study may help to decribe psychological and behavioral factors affecting resilience against age-related changes in the brain, cognition or mental health. This hopefully will generate ways of protecting healthy cognitive and mental aging in air-polluted environment, an approach that is needed, given the current limited progress specifically in preventing dementia [86] and the large number of people chronically exposed to poor air quality [6].

